### Procedures and interventions

When a potential participant (either group 1 or 2) meets with a research nurse, the study is explained and eligibility criteria are assessed. If he decides to participate, both the participant and research nurse sign two copies of an informed consent form, which includes a Patient Information Form; one copy is kept for our records and the other is given to the participant. Since Group 1 is followed up for 24 months, and participation in Group 2 only consists of a single visit, both procedures are explained separately below.

### Group 1

During the first visit (month 0), participants are asked to complete a short online questionnaire on an SHC-provided tablet (further explained in the Questionnaires section). Next, the nurse explains the sampling procedures, and the participant provides anal, penile and oral rinse self-samples. For the anal swab, participants insert the swab 3 cm into the anal canal and turn it around for 5–10 s. For the penile swab, participants rub the swab firmly over the skin of the penile shaft, including the outside of the foreskin, for 20 s (ie, 5 s per side). For the oral rinse samples, participants rinse their mouth with a saline solution for 30 s, collecting cells and viral particles from the oral cavity and oropharynx. Finally, the nurse collects 5 mL venous blood. If needed, the visit is combined with a regular STI visit (eg, PrEP consultation, STI tests or treatment). After sample collection, the first dose of the bivalent HPV vaccine, Cervarix, is administered. The next appointment (at month 6 and, if necessary, at month 1) is scheduled during this appointment.

At month 6, participants receive their last vaccine dose. Participants who missed a scheduled dose are contacted by phone and mail to reschedule the appointment as soon as possible. Samples for testing are collected neither at month 1 (for participants with HIV) nor at month 6. At month 15, participants complete a short online questionnaire about sexual behaviour and AEs. During the 24 month visit, participants are asked to complete the same online questionnaire and provide the same anal, penile, oral and blood samples as during the initial appointment. Participants who have missed their 6-month (or 1-month dose in case of immunocompromised individuals and people with HIV) vaccine dose are offered vaccination during the 24-month study visit. Study participation is completed after this visit. When all study visits are completed, participants interested in their serological response and anal HPV status will receive their results by mail, along with careful interpretation.

### Group 2

Group 2 will be recruited in the same calendar period when group 1 participants return for their 24-month visit. Men from group 2 will provide the same (anal, penile, oral gargle, venous blood) samples for HPV testing and complete the same questionnaire as group 1. Participation in group 2 consists of one single study visit.

### Adverse events

AEs are monitored through an online questionnaire, sent 2 weeks after administration of each vaccine dose (see the Questionnaires section below). Completed questionnaires are checked on a daily basis to identify any AEs that may be serious (SAEs). In the case of possible SAEs, the participant is contacted by telephone to obtain more details, and in some cases, asked to visit the clinic for further examination. SAEs will be reported to the sponsor (ie, Public Health Service (GGD) of Amsterdam) within 24 hours of obtaining knowledge of the events. The sponsor will report SAEs within 7 days to euclinicaltrials.eu, in accordance with international guidance. Symptoms that are severe will be followed up by the study physician with the assistance of the study nurse, until resolution or stability of the symptoms.

Information on AEs after vaccine administrations at 0 months, 1 month and 6 months (group 1) will be analysed as an additional study outcome. We will provide descriptive statistics of AEs.

### Data collection

#### Clinical data

We will obtain clinical data of all participants using both the medical records collected at the SHC and additional online questionnaires. The following data are collected: (1) demographics (age, gender at birth, highest educational level, work status, income, country of birth); (2) general health (including HIV status, STI history, use of alcohol, any drugs and tobacco), (3) sexual behaviour (age of sexual debut; age of anal sex debut; gender of sex partners; number of sex partners in previous 6 months; number of lifetime sex partners; number of anonymous sex partners in previous 6 months; position during anal sex (ie, insertive/receptive), condom use during anal sex).

#### Questionnaires

During the enrolment visit, participants of both groups are asked to complete a short baseline questionnaire on an SHC-provided tablet concerning above-mentioned topics. In addition, group 2 will be asked the reason for not yet being vaccinated against HPV and whether, if they were to be offered HPV vaccination at that visit, they would accept this offer. Furthermore, group 1 is asked to complete four additional (for a total of five) questionnaires (see figure 1 for overview). Participants of group 1 are asked to complete a brief online questionnaire 2 weeks after each vaccine dose, eliciting information regarding AEs. At month 15, participants of group 1 are asked to complete an additional online questionnaire on sexual behaviour and on AEs. All online questionnaires are sent by email. Participants who do not complete an online questionnaire within 7 days are sent a reminder with a new link. When participants come for a second or later study visit and they have not yet completed a previous online questionnaire, they are asked to complete the AE questionnaire at that visit. At the final visit for participants of group 1, a 24-month questionnaire will be administered with similar questions as during the enrolment visit (see online supplemental appendix I for all questionnaires).

#### Laboratory analyses

Anal, penile, oral gargle and venous blood samples are collected. Penile and oral gargles are stored for future analyses. Anal samples will be tested for HPV DNA at the Public Health Laboratory of the Public Health Service of Amsterdam. First, DNA will be extracted.^37^ Next, a broad-spectrum HPV DNA amplification will be performed using the HPV SPF10 DEIA/line probe assay (LiPA)25 system (Cerba Research; Paris; France). If HPV DNA is detected by the DEIA, it will be genotyped for 25 HPV genotypes (HPV-6, 11, 16, 18, 31, 33, 34, 35, 39, 40, 42, 43, 44, 45, 51, 52, 53, 54, 56, 58, 59, 66, 68/73/97, 70 and 74) using the LiPA.^38^ Positive hybridisation is exposed as purple bands on a blot, which will be independently interpreted by two readers. In case of discrepancies, a third reader will be decisive.^38^

Serum samples will be analysed for HPV-specific Immunoglobin G serum antibodies against L1 virus-like particles (VLP) of HPV types included in the vaccine. The analysis will be done using a VLP-based multiplex immunoassay at the Centre for Infectious Disease Control of the Dutch National Institute for Public Health and the Environment (RIVM).

### Sample size calculation

The sample size was calculated under the assumption that HPV vaccination of MSM aged 19–26 years will have similar efficacy against newly acquired HPV-16 and HPV-18 infections as among MSM with limited prior exposure to these types. We estimated the expected population-level VE in an MSM population attending the SHC in Amsterdam using assumed ‘true’ prophylactic vaccine efficacy from an existing trial^21^ and population-level characteristics of the MSM population at the SHC. Next, we determined the required sample size to demonstrate this expected VE at a significance level of 0.05 with 80% power.

For efficacy against newly acquired infections, we used per-protocol (PP) estimates of the quadrivalent HPV vaccine trial in US men.^21^ The PP population consisted of subjects who were seronegative on day 1 and PCR-negative throughout the 3-dose vaccine course for relevant HPV types. In PP analyses, a prophylactic efficacy of 84.5% (95% CI 63.1% to 94.6%) against anal detection of DNA of HPV-16 and/or HPV-18 at any time was estimated,^21^ which we took as efficacy against incident HPV-16 and HPV-18 DNA positivity in anal samples for our study. The sample size calculation was further informed by prevalence of anal HPV-16 and HPV-18 infections and seropositivity data from MSM participants in the PASSYON study. PASSYON is a biennial repeated (since 2009) cross-sectional study among SHC attendees aged 16–24 years, enrolled at nine SHCs throughout the Netherlands, among which was the SHC of Amsterdam (online supplemental table S1).^39 40^ Note that prevalence and seropositivity were higher in the PASSYON study than in the quadrivalent vaccine trial, reflecting a higher prior exposure to HPV. This is in line with the fact that >80% of the PASSYON participants reported >5 sex partners, whereas the preselected population in the quadrivalent vaccine trial was limited to men with ≤5 lifetime sex partners.

In sample size calculation, we made two assumptions. First, we assumed that anyone who tests positive for a vaccine type (either DNA-positive or seropositive) at baseline is not at risk for acquisition of that vaccine type during follow-up and second, that there are no latent or undetectable (DNA-negative) HPV infections at baseline (see figure 2). By powering our study to a scenario without latency, we aim to detect VE that is relevant for achieving substantial population-level impact in a targeted immunisation campaign. We previously concluded, based on a dynamic modelling study, that the efficiency of targeted vaccination would be severely reduced if latency were common among sexually experienced vaccine recipients.^28^ We deliberately did not power our study to capture diminished VE in such a scenario.

**Figure 2 F2:**
[figure not shown]
Expected HPV-16 population distribution among young MSM in a vaccinated and unvaccinated scenario. HPV, human papillomavirus; MSM, men who have sex with men.

Following these assumptions, we assume a baseline prevalence of 13.9% for HPV-16 and 11.3% for HPV-18 in both groups and calculated an expected 24-month DNA positivity of 6.2% for HPV-16 and 4.6% for HPV-18 in group 1. By using the χ^2^ test to compare the 24-month prevalence in group 1 against the baseline prevalence in group 2, a sample size of 264 for HPV-16 and 284 for HPV-18 is required for 80% statistical power. This corresponds with an OR of 0.41 for HPV-16 and 0.38 for HPV-18*,* which leads to an anticipated VE against anal HPV-16 and HPV-18 of 59% and 62%, respectively (see online supplemental table S1, figure S1 and appendix II for formula and calculations). The sample size was determined at 300 vaccinated and 300 unvaccinated MSM, to retain power when estimating VE in analyses with adjustment for potential confounders. In order to have complete data for 300 vaccinated men at month 24, with an expected loss to follow-up (LTFU) of 30% among group 1 participants, the target for inclusion was set at 430 participants in group 1. The 30% expected LTFU over 24 months is based on a similar previous study among MSM visiting the SHC, where 20% LTFU was observed.^41^

### Statistical analyses

#### Primary outcomes

Our main endpoint is type-specific VE against anal vaccine type infection, derived from the comparison of HPV-16 or HPV-18 DNA positivity in anal samples between group 1 participants at 24 months after vaccination and unvaccinated participants of group 2. VE will be estimated as 1–OR, where OR stands for the OR of HPV-16 DNA positivity in group 1 at 24 months relative to the HPV-16 DNA positivity of group 2. The use of ORs to estimate VE is suitable in this cross-sectional setting because it captures the joint effects of vaccination on the infection and clearance hazards,^42 43^ and our study is built on the premise that MSM may experience repeated events of HPV acquisition and clearance at a type-specific level. Prophylactic vaccination is anticipated to lead to reduced acquisition of new vaccine-type HPV infections, and our study is powered to detect a difference in vaccine-type DNA positivity due to this reduction.

Since our study is not randomised, the comparison between the two study groups and VE estimates may be affected by confounding factors. To address this, we will compare group 1 at month 24 and group 2 to identify possible differences between the groups that may lead to biased estimates. Groups will be compared using standard statistical tests. Continuous variables will be analysed using unpaired t-tests in case of normally distributed data, and Mann-Whitney’s U-tests in case of skewed data. For categorical variables, we will use χ^2^ tests or Fisher’s exact test in case of expected cell count less than five. Statistical significance will be considered at a significance level of 0.05 without correction for multiple testing. Variables with well-known effect on HPV risk (such as number of sex partners), and variables with significantly different distributions between both groups will be included in a regression model to obtain adjusted estimates of VE.

We will calculate adjusted ORs for HPV-16 and HPV-18 positivity using a logistic mixed model, adjusting for known variables that are associated with HPV positivity (all types) or vaccination status. This method has been used before to estimate type-specific VE of the bivalent HPV vaccine against cervicovaginal and anal HPV positivity in female SHC clients, with high concordance between both estimates.^27 44^

We will provide both intention-to-treat (ITT) and PP estimates of VE. In the ITT analysis, all individuals who are recruited into group 1 and return for the month 24 visit will be included. In the PP analysis, we will only consider group 1 participants who received all vaccine doses in the recommended intervals. Recommended intervals are 5–12 months after the first dose for the 6-month dose, and 3–6 weeks after dose 1 for the 1-month dose in immunocompromised individuals.^45 46^ In a sensitivity analysis, we will also calculate VE among the subgroup of PP participants with confirmed antibody response at month 24. Our primary analyses will be based on complete data for HPV-16/18 infection outcomes, using model-based imputation to handle any missing data for possible confounders (ie, covariates). In a sensitivity analysis, we will use model-based imputation for missing HPV-16/18 infection outcomes, to assess the effect of potential selective drop-out in Group 1 participants from baseline to month 24.

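### The only check on selective drop-out, model-based imputation of month-24 HPV results, corrects loss explained by recorded data but, as described, cannot show loss tied to unrecorded risk or to infection itself

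*Protocol article*

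**What the plan says.** Under Statistical analyses, Primary outcomes, the intention-to-treat set is limited to group 1 men who come back at month 24, and the primary analyses rest on observed HPV-16/18 outcomes. Imputation is used there only for covariates. Missing outcomes are handled in one sensitivity analysis: "we will use model-based imputation for missing HPV-16/18 infection outcomes, to assess the effect of potential selective drop-out in Group 1 participants". No other analysis in the article varies what is assumed about non-returners' infection status. The article gives no missingness assumption, no list of predictors and no departure scenario.

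The Sample size calculation sets the group 1 inclusion target "with an expected loss to follow-up (LTFU) of 30% among group 1 participants" and reports 20% loss in a similar earlier study. Group 2 attends once (Procedures and interventions), so it has no follow-up to lose. The Discussion names loss in group 1 as one of two key challenges.

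Non-returners are not blank records. The Group 1 procedures and Data collection sections give each of them a month-0 questionnaire, anal swab and blood sample. Some will also have answered the month-15 questionnaire on sexual behaviour.

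**The concern.** A model for month-24 positivity can only be fitted to men who have a month-24 swab. Unless a departure is specified, it gives a non-returner the positivity of a returner with the same recorded characteristics. Loss explained by those characteristics is corrected. Loss that depends on something not recorded, such as exposure after the last questionnaire, or on the month-24 infection itself, is assumed not to exist.

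The analysis is nevertheless assigned the task of assessing selective drop-out, without that limit. If the imputed VE lies close to the complete-case VE, readers may conclude that attrition does not matter, when only the recorded part of it has been examined. Because all the attrition is in the vaccinated group, any error enters one side of the comparison and nothing on the other side offsets it.

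**Working it through.** **Inputs (Protocol article, Sample size calculation).** Error rates: "at a significance level of 0.05 with 80% power". Prevalence without vaccination: "we assume a baseline prevalence of 13.9% for HPV-16 and 11.3% for HPV-18 in both groups". Group 1 at month 24: "expected 24-month DNA positivity of 6.2% for HPV-16 and 4.6% for HPV-18 in group 1". Target: "The sample size was determined at 300 vaccinated and 300 unvaccinated MSM". Loss: 30% planned, 20% seen earlier. Inclusion target: 430.

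**The plan's own figures reproduce.** A two-sided 5% chi-square comparison with 80% power and continuity correction gives 264 and 284 per group, matching "a sample size of 264 for HPV-16 and 284 for HPV-18 is required for 80% statistical power" (239 and 255 without the correction). For HPV-16, OR = (0.062/0.938)/(0.139/0.861) = 0.41. For HPV-18, OR = (0.046/0.954)/(0.113/0.887) = 0.38. These agree with "This corresponds with an OR of 0.41 for HPV-16 and 0.38 for HPV-18". Allowing for loss, 300/0.70 = 429, against the stated 430.

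**Shifted scenarios.** At 30% loss, 430 men split into 301 returners and 129 non-returners; at 20%, into 344 and 86. Let p_R be returners' positivity, p_N non-returners' positivity, p_U group 2's prevalence and D the odds multiplier (an assumption; the article gives none).

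- odds(p_N) = D × odds(p_R)
- p_all = (301 p_R + 129 p_N)/430
- VE = 1 − odds(p_all)/odds(p_U)

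Example, HPV-16 with D = 2: p_N = 0.117, p_all = (301 × 0.062 + 129 × 0.117)/430 = 0.078, OR = 0.53, VE = 47%.

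| Non-returners | HPV-16, 30% loss | HPV-16, 20% loss | HPV-18, 30% loss | HPV-18, 20% loss |
|---|---|---|---|---|
| D = 0.5 | 65% | 63% | 68% | 66% |
| D = 1 | 59% | 59% | 62% | 62% |
| D = 1.5 | 53% | 55% | 57% | 58% |
| D = 2 | 47% | 51% | 51% | 55% |
| D = 3 | 36–37% | 44% | 41% | 48% |
| Group 2's prevalence | 42% | 48% | 44% | 50% |

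**Confidence limits by the multiple-imputation (Rubin) rules**, many imputations, on the log odds ratio:

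- Within: W = 1/[430 p_all(1−p_all)] + 1/[300 p_U(1−p_U)]
- Between: B = (129/430)² × [g² p_R(1−p_R)/301 + p_N(1−p_N)/129] / [p_all(1−p_all)]², where g = p_N(1−p_N)/[p_R(1−p_R)] for a multiplier and g = 0 when p_N is set to a fixed value
- SE = √(W + B)

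For HPV-16 at 30% loss:

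- D = 1: SE 0.292, 95% CI about 28% to 77%.
- D = 2: SE 0.290, lower limit 1 − 0.527 × exp(1.96 × 0.290) = about 7%.
- Group 2's prevalence: SE 0.267, lower limit 1 − 0.576 × exp(1.96 × 0.267) = about 3%. If 13.9% is instead treated as known and only the returners' and group 2's sampling error is carried, SE is 0.209 and the lower limit about 13%.

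**Tipping point.** The lower limit reaches zero at D = 2.36 (HPV-16) and 2.35 (HPV-18) with 30% loss, and at 3.37 and 3.35 with 20% loss. Other reasonable variance formulas give 2.33 to 2.37 and 3.30 to 3.40. For VE itself to be zero at 30% loss, about 32% (HPV-16) or 27% (HPV-18) of non-returners would have to be positive, for example (0.139 − 0.7 × 0.062)/0.3 = 0.32.

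**What the imputation does and does not reveal.** A simulation of 2,000,000 men used about 33% missing outcomes, one recorded and one unrecorded risk factor, each present in 40% and each with a log odds ratio of 1.2 for infection. Group 2 was set at 13.9%. The effect sizes are illustrative.

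| Drop-out driven by | Complete-case VE | Imputed VE | True VE |
|---|---|---|---|
| Recorded factor only | 58% | 51% | 51% |
| Unrecorded factor only | 58% | 58% | 51% |
| Both | 59% | 56% | 52% |

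The check works fully in the first case, shows nothing in the second, and shows part of the bias in the third.

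**The case against.** The planned analysis is far from empty. Baseline type-specific DNA and antibody status are likely to be strong predictors of month-24 positivity, and the Secondary outcomes section plans to estimate that relation. Drop-out linked to them would be both shown and corrected. A reader might infer that imputation leaves VE unchanged whenever non-returners differ in unmeasured ways, or that it cannot show selective drop-out at all. The documents do not support that: VE stays put only when the cause is wholly unrecorded.

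The article also does not say that data are assumed missing at random. Model-based imputation does not exclude a departure model, and the analysis plan, which is not shown, may contain one. This stands, and it limits the point to the analysis as the article describes it. Predictor lists and imputation settings are properly left to the analysis plan and are not criticised here. What remains is that the article gives one analysis a purpose that it meets only in part.

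Three cautions on size also stand. The 30% is a planning allowance, not observed loss. The direction is unknown: month-24 visits can be combined with regular STI visits, so returners could be the higher-risk men, and at half the odds HPV-16 VE would rise to 65%. The figures are unadjusted, whereas the planned VE is covariate-adjusted, which may absorb part of a behavioural difference.

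A reader might also infer that setting HPV-16 non-returners to group 2's prevalence takes the lower limit below zero. That result (about −2%) comes only from reusing the unshifted SE of 0.292. With a variance suited to the scenario, the limit is about 3% to 13%.

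**Conclusion.** The point holds in limited form. The one drop-out analysis in the article addresses loss explained by recorded data. It leaves untested any loss related to unrecorded later risk or to month-24 infection, and all of that loss falls on group 1. If non-returners had twice the returners' odds of positivity for wholly unrecorded reasons, HPV-16 VE at 30% loss would be about 47% rather than 59%, and HPV-18 VE about 51% rather than 62%, with no sign of it in the planned check. The conclusion of a positive VE would be lost at a multiplier of about 2.3 to 2.4, or 3.3 to 3.4 at 20% loss.

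This rests on the planning prevalences, 300 controls, unadjusted odds ratios and assumed multipliers. Nothing in the documents says that drop-out will be selective to this degree, or in which direction. The point is a worthwhile and cheap improvement to the sensitivity analysis; it does not show that the primary estimate is wrong.

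**What to change.** Keep the imputation, with month-0 type-specific DNA, serology and behaviour and the month-15 behaviour data among its predictors. Repeat it with non-returners' odds of positivity multiplied over a two-sided range, for example 0.5, 1, 1.5, 2 and 3, and once more with non-returners at group 2's prevalence. Compute the variance by the multiple-imputation rules separately in each scenario. Report VE with its interval for each type and scenario, and the multiplier at which the lower 95% limit reaches zero. Describe the unshifted run as correcting only for loss explained by recorded data. If the analysis plan already contains such scenarios, a cross-reference and that description are enough.

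The cost is a paragraph in the analysis plan and a loop around code already intended; no new data are needed. The downside is slightly more analysis and a VE that may appear less robust.
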